## Methods

### Design

To determine the effectiveness of adding E-TRAIN to CBT, we will conduct a multicenter two-arm randomized controlled trial (RCT) using a two-arm parallel group design. We aim to include 138 adolescents with a primary diagnosis of depressive and/or anxiety disorder. After completion of baseline assessment (T0), participants will be allocated to either CBT or CBT + E-TRAIN. Follow-up assessments will take place after 3 (T1), 6 (T2: primary outcome), and 12 months (T3) post-baseline assessment. See Fig. 1 for the trial flowchart. All assessments are online questionnaires, which will be completed by multiple informants (adolescents, parents/caregivers, and therapists), except for the Mini (KID) International Neuropsychiatric Interview (MINI version 7.02) [54, 55], which will be assessed in a telephone interview 6 months after baseline. This protocol was written in accordance with the Standard Protocol Items: Recommendations for Interventional Trials (SPIRIT) guideline [56]. This study has been registered in the Netherlands Trial Register (NL9564). The Medical Research Ethics Committees United (MEC-U) in the Netherlands has approved the study protocol.

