### Sample size

We will conduct a pairwise comparison between the treatment arms (CBT + E-TRAIN vs. CBT). The continuous primary outcome measures will be depressive and anxiety symptoms at T2. A priori sample size calculation was performed using the *sampsi* command in Stata (version 14.0; Stata Corp, College Station, USA). We aim to include *N* = 138 adolescents (*n* = 69 in each group) to be able to detect a Cohen’s d of 0.40 with α = 0.05 (two-sided) and power = 0.80, taking into account 35% extra inclusion to account for drop-out.

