#### Randomization

After baseline assessment has been completed by the adolescent, randomization will be carried out. Randomization of participants will be performed via Castor EDC (Castor Electronic Data Capture (2021.2)) by a researcher who is blind to block size and order. Randomization will take place at an individual level, stratified by primary diagnosis (depressive or anxiety disorder) and treatment site using a computer-generated block randomization schedule. To ensure that an equal number of patients are allocated to CBT and CBT + E-TRAIN, the allocation ratio will be 1:1. To prevent selection bias, all researchers will be blind to random block order. No researchers will have access to the randomization schedule. Due to the nature of the add-on design, blinding of adolescents, parents, therapists, and researchers to treatment condition is not applicable. The research assistants assessing the diagnostic interview at T2 will be blinded to treatment condition.

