### Data analyses

#### Primary outcome measures

Linear mixed models will be used to determine the effectiveness of adding E-TRAIN to CBT in reducing depressive and anxiety symptoms (measured with the RCADS25). A two-level structure will be used (Level 1: repeated measures, Level 2: patients). The overall treatment effect will first be evaluated in a model with condition and the baseline value of the outcome. Second, between-group differences at each time-point will be examined by adding time and the interaction of time and condition to the model. Time will be treated as a categorical variable, represented by dummy variables. Furthermore, as a sensitivity analysis, we will fit a model adjusted for the total number of completed CBT sessions and other potentially relevant confounders. Imputation of missing data will not be necessary because we will use mixed-model analyses, which adequately handles missing values [98]. Analyses will be conducted on the entire randomized sample (i.e. intention to treat) and on the per protocol/treatment completers sample. For the treatment completers sample of the experimental (E-TRAIN) condition, adolescents who completed ≥ 66% of the online sessions (four sessions or more) will be regarded as completers. The aforementioned main analyses will also be conducted separately for those with a primary diagnosis of depressive disorder, and for those with a primary diagnosis of anxiety disorder. Analyses will be conducted using SPSS version 26 + and R version 3.0 + . Statistical significance will be set at α < 0.05.

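### The overall-effect model has no time term, so the statement that mixed models take care of missing values does not hold for it when the arms lose late visits unequally

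*Protocol article*

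**What the plan says.** The section on analysis of the primary outcome describes a two-step linear mixed model for the RCADS25, with repeated measures nested in patients. Step one: "The overall treatment effect will first be evaluated in a model with condition and the baseline value of the outcome". Step two adds categorical time and its interaction with condition, to give the between-group difference at each visit. The Design section sets the visits: "Follow-up assessments will take place after 3 (T1), 6 (T2: primary outcome), and 12 months (T3) post-baseline assessment".

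The missing-data statement follows in the same paragraph: "Imputation of missing data will not be necessary because we will use mixed-model analyses, which adequately handles missing values". It draws no line between the two steps and names no missing-data assumption. The section on secondary outcomes carries the same procedures over. The Sample size section expects loss: "taking into account 35% extra inclusion to account for drop-out".

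**The concern.** A likelihood-based mixed model gives valid estimates under missing-at-random only if its mean structure is right. Step one assumes one mean per arm across all follow-up visits, given baseline. If scores go on changing between T1 and T3, that mean is wrong, and an arm's estimate depends on which visits were observed. An arm that loses more late visits leans on its early ones, and the gap appears in the condition coefficient although treatment did nothing.

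At stake is the overall treatment effect, which the plan evaluates first and repeats for the secondary outcomes. The same sentence that dismisses imputation would reassure a reader about an estimate it does not protect.

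**Working it through.** **Inputs from the article.** Sample size: "138 adolescents (*n* = 69 in each group". Design effect, used here only as a yardstick: "d of 0.40 with α = 0.05 (two-sided) and power = 0.80". Allocation: "the allocation ratio will be 1:1". Three follow-up visits.

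**Planned loss.** Read as 35% added to the required number, 69/1.35 = 51.1, so 51 per arm are expected to remain. The loss is 18/69 = 26.1% per arm, or 35% if the figure is read as a drop-out rate. The article gives one allowance and no retention by arm. (The unadjusted two-sample formula for the stated effect, alpha and power gives 99 per arm, not 51. An assumed baseline correlation of 0.70 gives 99 × (1 − 0.49) ≈ 51. Nothing below depends on this.)

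**Assumptions, not in the article.** No true effect; mean change from baseline of -0.4, -0.8 and -1.0 SD at T1, T2 and T3 in both arms; drop-out monotone and random within arm; residual correlation ρ between visits of 0.3 to 0.7.

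**Formula.** In a random-intercept model without time, a patient seen at the first k visits has weight w_k = k/(1 + (k − 1)ρ) and contributes the average m_k of the first k means. With p_k the share of the arm with exactly k visits, the arm mean is Σ p_k w_k m_k / Σ p_k w_k.

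**Worked case, ρ = 0.5.** Weights: 1, 1.333, 1.5. Averages: -0.4, -0.6, -0.7333. Retention at T1/T2/T3 is 95/84/80% in one arm and 95/64/55% in the other.

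- Lower-loss arm: p = 0.11, 0.04, 0.80. Numerator -0.044 − 0.032 − 0.880 = -0.956; denominator 0.110 + 0.0533 + 1.200 = 1.3633; mean -0.701.
- Higher-loss arm: p = 0.31, 0.09, 0.55. Numerator -0.124 − 0.072 − 0.605 = -0.801; denominator 0.310 + 0.120 + 0.825 = 1.255; mean -0.638.
- False difference: -0.638 − (-0.701) = 0.063 SD, which is 0.063/0.40 = 16% of the design effect. For ρ of 0.3 and 0.7 it is 0.055 and 0.069.

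With identical retention the two arm means coincide and the difference is exactly 0.

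**Simulation.** 69 per arm, no true effect, same means, random-intercept REML. The first two rows assume a correlation of 0.5 between measurements (4,000 runs), the others 0.6 (2,000 runs).

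| T3 retention | False difference, no time | Type I error, no time | With time dummies |
|---|---|---|---|
| 83% vs 63% | 0.034 SD | 5.9% | 0.001–0.002 SD; 4.8–5.0% (rows 1 and 2 together) |
| 85% vs 60% | 0.048 SD | 6.5% | as above |
| 80% vs 55% | 0.057 SD | 8.4% | 0.001 SD; 4.9% |
| 74% vs 60% | 0.030 SD | 5.6% | -0.002 SD; 4.6% |
| 68% vs 68% | 0.002 SD | 5.4% | 0.002 SD; 5.1% |

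In a more extreme case (T3 retention 85% vs 45%) the no-time model gives 0.074 SD and 9.8%. If drop-out in the 80% vs 55% case is missing-at-random rather than completely random, the no-time model is still off by 0.055 SD (6.6%); with time the error is 0.000 SD.

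**The T2 contrast from step two.** In the 80% vs 55% case it shows 0.003 SD and a type I error of 4.5%, so it is unaffected.

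**Direction.** Scores fall over time, so the arm losing more late visits looks worse. More loss under E-TRAIN works against E-TRAIN; more loss under CBT alone favours it.

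**The case against.** The primary outcome is the RCADS25 at six months. That contrast comes from step two, which already contains time and its interaction with condition. This stands: a reader might infer that the primary result is biased, and the article does not support that.

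The bias also needs two things the article does not state: unequal loss of assessments and continuing change after T1. The Discussion's remark on drop-out in internet-based treatment concerns adherence, and the reminders and vouchers for assessments do not differ by arm. This stands too, so the figures are conditional. They do not remove the defect, because the missing-data sentence is unconditional and the time-free model is specified outright.

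Two stronger readings are tempting. One is that the plan fails by having no analysis that departs from missing-at-random. The article condenses a fuller plan, and such an analysis is commonly left to the SAP, which is not shown; its absence here is no finding. Calling imputation unnecessary for a likelihood-based main analysis is also standard under missing-at-random. The other is that adolescents without any follow-up contradict the promise "Analyses will be conducted on the entire randomized sample (i.e. intention to treat". They do contribute nothing to a model that uses baseline as a covariate. But the phrase is set against the completers analysis, and under missing-at-random given baseline and arm the omission does not bias the T2 contrast.

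**Conclusion.** The concern holds for the overall-effect model only. As written, that model can turn unequal late drop-out into an apparent treatment difference, and the assurance about missing values is wrong for it. Under the assumed trajectory and T3 retention gaps of 20 to 25 points, the simulated error is about 0.03 to 0.06 SD, roughly 8 to 14% of the design effect (0.034/0.40 to 0.057/0.40), with type I error of about 6 to 8%. With a 14-point gap type I error is close to nominal (5.6%), and with equal loss there is no bias. The sign depends on which arm loses more. Trajectory, correlations and retention by arm are all assumptions. This is a small, avoidable flaw in a stated model, not a threat to the six-month comparison.

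**What to change.** Add categorical time (dummies) to the overall-effect model, so that step one has condition, baseline and time, and step two adds only the interaction. Do the same for the secondary outcomes with repeated follow-up; the diagnostic interview is held only at T2 and needs no time term. Reword the imputation sentence to say that the mixed models are valid without imputation under missing-at-random, provided time is in the model.

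A delta-adjusted sensitivity analysis at T2 is optional and may already be in the SAP. The cost is a change of wording and one extra model term, with no new data and no change to the sample size.

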E-TRAIN will be provided on a secured online platform (*Jouw Omgeving*). It consists of six sessions in which six ER skills are covered: 1) relaxation; 2) non-judgmental awareness of emotions; 3) acceptance of emotions; 4) self-support; 5) analyzing emotions; and 6) modifying emotions. Adolescents receive psycho-education about these skills, and about the origin and functions of emotions in animated videos (of 1–5 min). Moreover, each session includes short written texts, exercises, relevant examples, patient stories, and audio files. By listening to these audio files, the adolescent can practice with the newly acquired ER skill and previously acquired skills. After each session, the adolescent is stimulated to listen to this audio file at least three more times before the next session as a homework assignment. See Fig. 2 for more detailed information on each session. Each E-TRAIN session will take approximately 25 min to complete. After each session a trained therapist will provide feedback on the exercises, using a secured chat function within the online platform, to guide the adolescent in correctly applying the learned ER skills.

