#### Treatment as usual: CBT

Both groups will receive CBT, a commonly used evidence-based therapy for adolescents with anxiety [61] and depression [62, 63]. CBT will be provided by experienced MSc or registered Health Care psychologists. The primary goal of CBT is to identify and restructure maladaptive thought patterns and behaviors (e.g., [64, 65]). Key components of CBT for adolescents with depressive and anxiety disorders are 1) psychoeducation; 2) behavioral activation, exposure, and behavioral experiments; 3) cognitive restructuring; and 4) relapse prevention [65, 66].

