##### Therapist measures

The CBT therapist of each participant will be asked to report the following: number of CBT sessions, content and number of sessions of non-CBT care. Additionally, the E-TRAIN therapist will be asked to fill in an adapted version of the System Usability Scale to measure the usability of the online intervention (SUS) [97].

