## Discussion

This paper describes the study protocol of a randomized controlled trial aimed at assessing the effectiveness of the addition of a guided internet-based emotion regulation training (E-TRAIN) to CBT in reducing depressive and anxiety symptoms in adolescents with a depressive or anxiety disorder compared to CBT alone. Given the high prevalence and undesirable effects of anxiety and depressive disorders in adolescents, it is of great importance to improve treatment outcomes of these patients. Dysfunctional emotion regulation appears to be an important target of intervention in adolescents with aforementioned disorders, and adolescence appears to be a critical time period to enhance emotion regulation strategies. To the best of our knowledge, this study is the first to examine the effectiveness of a guided online emotion regulation intervention in adolescents with a depressive or anxiety disorder. We will investigate whether treatment outcome of CBT may be improved by strengthening ER skills in this vulnerable population. Moreover, this study will enhance knowledge on ER and its associated factors in adolescents with depression and anxiety.

Strengths of the current study are its randomized design and the relatively long follow-up period of 12 months. Another strength is the large battery of clinically relevant and validated outcome measures that are administered by multiple informants at multiple assessments. An important concern in the field of e-health research is treatment adherence, since internet-based treatments generally are associated with high dropout levels (e.g., [47]). It is expected that the relatively small amount of E-TRAIN sessions, three video conference sessions and weekly guidance of the therapist will enhance treatment adherence. However, this will remain an important challenge of this trial.

If this study provides evidence for the effectiveness of E-TRAIN, it can be an important addition to mental health care for adolescents with depressive and/or anxiety disorder.

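### The only stated completer rule is E-TRAIN session attendance, which can exclude patients from one arm only, so the per-protocol contrast is open to post-randomisation selection bias, probably but not certainly favouring E-TRAIN

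*Protocol article*

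**What the plan says.** Under Data analyses, Primary outcome measures, the protocol article states: "Analyses will be conducted on the entire randomized sample (i.e. intention to treat) and on the per protocol/treatment completers sample". One completion rule follows. It is introduced by "For the treatment completers sample of the experimental (E-TRAIN) condition" and reads "adolescents who completed ≥ 66% of the online sessions (four sessions or more) will be regarded as completers". The E-TRAIN section gives the denominator: "It consists of six sessions in which six ER skills are covered".

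No completion rule is stated for CBT alone, and no CBT-attendance rule for either arm. Yet CBT is common to both ("Both groups will receive CBT"), and its dose is recorded for everyone ("The CBT therapist of each participant will be asked to report the following: number of CBT sessions"). In the analysis, CBT dose appears only as a covariate: "we will fit a model adjusted for the total number of completed CBT sessions and other potentially relevant confounders".

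The article calls that covariate-adjusted model a sensitivity analysis. It gives the completer analysis no such label and does not rank it against intention to treat. The Secondary outcome measures section applies the same procedures to the secondary outcomes, so the completer contrast is repeated there.

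**The concern.** Completing four or more modules happens after randomisation and can depend on motivation, early course of symptoms, family support and severity. The rule takes low adherers out of the E-TRAIN arm. Their counterparts in the CBT arm, who would not have finished the modules had they been offered them, cannot be identified and are not removed by any stated rule. The two groups then differ in more than treatment, and randomisation no longer protects the comparison.

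At stake is how a secondary result is read. A favourable completer estimate beside a null intention-to-treat estimate could be taken as evidence that E-TRAIN works for those who do it, when selection alone could produce it. The Discussion itself notes that "internet-based treatments generally are associated with high dropout levels" and regards adherence as a challenge for this trial.

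**Working it through.** **The plan's own figure.** 0.66 × 6 = 3.96, so four sessions, and 4/6 = 66.7%. The threshold is internally consistent. The issue is where it applies.

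**Inputs.**
- From the article: 69 per arm, design effect d = 0.40, two-sided 5% level (Sample size).
- Number analysed at T2: 69/1.35 = 51 per arm, reading the 35% extra inclusion as a multiplier. Results for 69 are shown as well. The bias does not depend on this number; only the false-positive rate does.
- Assumed, because the article gives neither: p, the share completing at least four sessions, and ρ, the correlation between propensity to complete and a good outcome *that remains after baseline adjustment*. The planned model includes the baseline value of the outcome, so selection captured by baseline RCADS25 must not be counted in ρ.

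**Formulas.** True effect zero, normal propensity and outcome with unit variance, selection in the E-TRAIN arm only, n patients per arm before selection:
- λ = φ(z_p)/p, where z_p is the p-quantile and φ the density of the standard normal
- bias = ρ × λ
- variance in the completer group: v = 1 − ρ²λ(λ + z_p)
- SE = √(v/(np) + 1/n)
- two-sided false-positive rate = 1 − Φ(1.96 − bias/SE) + Φ(−1.96 − bias/SE)

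**Central case, p = 0.70, ρ = 0.3, n = 51.** λ = 0.348/0.70 = 0.497. Bias = 0.3 × 0.497 = 0.15 SD. v = 0.954. SE = √(0.954/35.7 + 1/51) = 0.215. False-positive rate = 10.6%.

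| p | ρ | bias toward E-TRAIN (SD) | share of 0.40 | false-positive rate, n = 51 | n = 69 |
|---|---|---|---|---|---|
| 0.80 | 0.2 | 0.07 | 17% | 6.3% | 6.8% |
| 0.70 | 0.3 | 0.15 | 37% | 10.6% | 12.7% |
| 0.60 | 0.4 | 0.26 | 64% | 21.3% | 27.1% |
| 0.70 | 0.1 | 0.05 | 12% | 5.6% | 5.8% |
| any | 0 | 0 | 0% | 5.0% | 5.0% |
| 0.70 | −0.2 | −0.10 | −25% | 7.4% | 8.3% |

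The SD here is the SD left after baseline adjustment. If 0.40 is in raw SDs and baseline correlates r with outcome, the shares shrink by √(1 − r²). For example, an assumed r of 0.5 gives a factor of 0.87.

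**Would a CBT rule repair it?** If the same selection (same p and ρ) acted in both arms, the biases would cancel. A CBT-attendance rule for controls only would select on a different behaviour. Applied to both arms, it would leave the four-session rule as an extra filter in one arm. In either case the asymmetry shrinks but does not disappear.

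**The case against.** The case against making much of this has several parts.

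- **Direction.** A reader might infer that the analysis is biased toward E-TRAIN as a matter of fact. The article gives no adherence rate and no link between adherence and prognosis. If early improvers stop the modules, the sign reverses, as the last row of the table shows. This objection stands; only a probable direction can be claimed.
- **Controls.** A reader might infer that all controls stay in the completer sample. The rule is worded for the experimental arm and says nothing about controls. A CBT rule may exist in the full protocol or analysis plan, and its absence from an article is not a defect. This stands too. The point rests on the rule that is stated, and the previous step shows that a CBT rule would not remove the asymmetry while that rule operates in one arm.
- **Size of the excluded group.** The Discussion's remark on dropout concerns internet-based treatments generally. The article expects the small number of sessions, the video contacts and the therapist guidance to help adherence. It still names adherence as a challenge, but a large excluded group cannot be inferred.
- **Baseline adjustment.** It removes selection carried by the baseline score. Motivation and early course remain. At ρ = 0.1 the effect is negligible.
- **Intention to treat.** It is planned, listed first and untouched. A completer analysis beside it is common practice. This limits the weight of the point but does not protect the completer contrast, which the article does not label as supportive.

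**Conclusion.** The point holds in limited form. As written, the per-protocol contrast is open to selection bias because its only stated rule can exclude patients from one arm alone. With no true effect, 60-80% completion and a residual correlation of 0.2-0.4, the spurious benefit would be about 0.07-0.26 SD, with a false-positive rate of about 6-21% at 51 per arm. These inputs are assumptions and the figures are an illustration, not an estimate for this trial. The documents do not support the stronger conclusions that the trial's main result is compromised or that the completer result must favour E-TRAIN. It is worth changing because the remedy mainly needs data already being collected.

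**What to change.** 1. Label the completer comparison supportive or descriptive, for the primary and secondary outcomes, and state how the control arm is handled in it.
2. Estimate the effect of receiving E-TRAIN as a complier-average causal effect at T2 in all randomised adolescents. Use randomisation as instrument, baseline RCADS25 and the stratification factors (primary diagnosis, site) as covariates, and the same missing-at-random handling of T2 drop-out as the main model. E-TRAIN was built for this study and runs on a secured platform, which supports treating non-compliance as one-sided.
3. Use any E-TRAIN exposure, from the platform logs listed under Adolescents in the E-TRAIN group, as the main compliance definition. Say whether the opening video contact counts as exposure and where it is recorded.
4. Report the four-or-more-session version as a sensitivity analysis, stating that it assumes no effect of fewer sessions. If a share q attends fewer than four sessions and gains an effect e, the estimate for a completing share p is inflated by (q/p) × e.

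**Cost.** Extra analysis and a wider interval. The standard error is roughly that of intention to treat divided by the compliance rate. In unit-variance terms with 51 per arm, intention to treat has √(2/51) = 0.198. At an assumed compliance of 0.70 this becomes 0.198/0.70 = 0.28, against 0.215 for the naive completer contrast in the central case. At an assumed compliance of 0.90 it is 0.22.

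### Separate analyses by primary diagnosis, with no condition by diagnosis term, cannot show whether the effect differs between depressive and anxiety disorder

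*Protocol article*

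**What the plan says.** The protocol article, Methods, Data analyses, Primary outcome measures, sets out a two-level linear mixed model for the RCADS25. It is fitted first with condition and the baseline value. Then "between-group differences at each time-point will be examined by adding time and the interaction of time and condition to the model". No other interaction is named.

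The same paragraph adds the diagnosis analyses: "The aforementioned main analyses will also be conducted separately for those with a primary diagnosis of depressive disorder". It plans the same for primary anxiety disorder. It closes with "Statistical significance will be set at α < 0.05", with no different rule for the diagnosis groups and no label such as exploratory or descriptive. The next section, Secondary outcome measures, says that the procedures just described also apply to the secondary outcomes.

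Under Randomization, allocation is "stratified by primary diagnosis (depressive or anxiety disorder) and treatment site", so primary diagnosis is recorded for everyone before allocation. Under Sample size, the target is a "Cohen’s d of 0.40 with α = 0.05 (two-sided) and power = 0.80" for the overall comparison of the two arms. No sample size is given for either diagnosis, and the expected split between diagnoses is not stated.

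**The concern.** Each separate model asks whether there is an effect within one diagnosis. Neither asks whether the effect is different in the other. That is a question about the difference between two effects, and it needs its own estimate and standard error.

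Placing two p-values side by side invites the conclusion that the training works in one diagnosis and not in the other whenever one falls below 0.05 and the other does not. Each group holds only part of a sample sized for the whole, so such a split result is likely even when the two effects are equal.

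The question matters in this trial. The Background motivates the intervention by describing emotion regulation as a factor shared by depressive and anxiety disorders, and both are enrolled. A split pair of p-values could lead readers to restrict the training to one diagnosis without evidence that the effects differ.

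**Working it through.** **Inputs from the article.** d = 0.40, two-sided α = 0.05, power 0.80, 69 per arm (138 in total), 35% extra inclusion for drop-out (Sample size); 1:1 allocation, stratified by primary diagnosis (Randomization).

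**Assumptions not in the article.** Share s of the sample with one of the two primary diagnoses: 0.5, 0.6 or 0.7. Equal true effect, equal outcome variance and equal drop-out in both diagnoses. One contrast tested per diagnosis.

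**The plan's own figure.** With d = 0.40 and no baseline adjustment, n per arm = 2 × (1.960 + 0.842)² / 0.40² = 98.1, so 99 before drop-out. This is not 69. The stated total is recovered only by assuming a baseline correlation that the article does not give: with r = 0.70, 98.1 × (1 − 0.49) = 50.04, so 51 per arm, and 51 × 1.35 = 68.9, so 69. That is a separate matter. Here the stated 80% power is taken at face value first, and relaxed afterwards.

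**Power within each diagnosis.** With 80% overall power, the expected z-value for the full sample is λ = 1.960 + 0.842 = 2.802. A group with share s has expected z-value λ√s, so its power is Φ(λ√s − 1.96) plus a negligible opposite tail. The two groups contain different participants, so their tests are independent and P(exactly one significant) = p₁(1 − p₂) + p₂(1 − p₁).

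| Split | p₁ | p₂ | Exactly one | Both | Neither |
|---|---|---|---|---|---|
| 50:50 | 0.508 | 0.508 | 0.500 | 0.259 | 0.242 |
| 60:40 | 0.583 | 0.425 | 0.512 | 0.248 | 0.239 |
| 70:30 | 0.650 | 0.335 | 0.549 | 0.218 | 0.233 |

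For example, at 60:40: 0.583 × 0.575 + 0.425 × 0.417 = 0.335 + 0.177 = 0.512.

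**Sensitivity to the stated power.**
- With 51 analysed per arm and no baseline adjustment, overall power for d = 0.40 is 52%. Exactly one group is then significant in 42–44% over the same splits.
- With a t-test on 25 per arm in each diagnosis and assumed baseline correlations of 0, 0.5 and 0.7, power per diagnosis is 0.283, 0.360 and 0.492. The chance of a split result, 2p(1 − p), is 0.41, 0.46 and 0.50.
- With no effect in either diagnosis, it is 2 × 0.05 × 0.95 = 0.095.

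**The interaction test.** When the two effects are equal, it rejects in 5% of trials by construction. For a between-diagnosis difference as large as the whole design effect, the standard error of the difference is the full-sample standard error divided by √(s(1 − s)). The expected z-value is therefore λ√(s(1 − s)): 1.401, 1.373 and 1.284 at 50:50, 60:40 and 70:30. Power is 0.288, 0.279 and 0.250.

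**The case against.** The strongest reply is that the article never proposes to compare the diagnoses. It says only that the analyses will also be run separately, and none of its three research aims concerns effect modification. A reader might infer that the plan tests for a diagnosis-specific effect by setting one significance result against the other. The text does not say so, and this stands: the harm lies in a later reading that the plan leaves open.

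It can also be said that an interaction test, an exploratory label and a multiplicity rule are details a full analysis plan may add. That would answer a complaint of missing detail. It does not fully answer this one, because the article does fix how diagnosis will be examined, and the method it fixes is the less informative one.

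Four further readings are tempting and not supported:
- **That separate variance estimation is an error.** It is not; it avoids assuming equal variances across diagnoses.
- **That stratifying by diagnosis makes the separate analyses worse.** Stratification helps, by protecting balance within each diagnosis.
- **That power per diagnosis is only 28%.** That figure ignores the planned baseline adjustment and implies overall power near 52%, not the stated 80%. On the stated power, each half of an even split has about 51%.
- **That the article calls the training itself transdiagnostic.** It uses the word for emotion regulation.

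Finally, the interaction test is weak here. That is true, and it argues for reporting an interval, not for relying on two separate verdicts.

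**Conclusion.** The point holds as a weakness in a supplementary analysis. The article commits to separate within-diagnosis tests at 0.05, extends them to the secondary outcomes, and names no term that compares the diagnoses. With the same true effect in both and the stated 80% overall power, exactly one diagnosis would be significant in about 50–55% of trials, against 5% false signals from an interaction test. The 50–55% rests on assumed splits of 50:50 to 70:30 and on equal variance and drop-out in the two groups. If overall power is lower than stated, the figure falls to about 41–50% over the range tried, which leaves the conclusion unchanged.

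The documents do not support saying that the trial will draw a false conclusion about one diagnosis, nor that its main result is compromised. The primary comparison uses the full sample and is unaffected.

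**What to change.** Replace the separate runs, or supplement them, with one full-sample mixed model containing condition, time, primary diagnosis and their interactions, together with the baseline value. Diagnosis-specific variances can be allowed if wanted. From that model, report the condition by diagnosis contrast at T2 and the T2 effect within each diagnosis, all with 95% CIs. Label these results supplementary or exploratory, apply the same approach to the secondary outcomes, and state that separate p-values will not be used to claim an effect in only one diagnosis.

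The cost is a change of wording and analysis code. No participants, visits or data are added, because primary diagnosis is already a randomisation factor. The limitation should be stated alongside: with about 25–29% power for a difference as large as the whole design effect, a non-significant interaction does not show that the effects are equal, and the interval carries the information.
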